**INTERVENTION:**					
Web-based intervention *Selfapy* for bulimia nervosa			*+*	*+*	
Waiting time			*+*	*+*	
**ASSESSMENTS:**					
**Primary confirmatory outcome**					
Number of Binge Eating and Compensatory Behavior Episodes (EDE-Q)		*+*		*+*	*+*
**Secondary confirmatory outcomes**					
Eating Disorder Examination Questionnaire (EDE-Q)		*+*		*+*	*+*
Weekly Occurrence of Binge Eating Episodes (WBQ)		*+*	*+*	*+*	*+*
Clinical Impairment Assessment (CIA)		*+*		*+*	*+*
*i*MTA Productivity Cost Questionnaire (*i*PCQ)		*+*		*+*	*+*
World Health Organization Well-Being Index (WHO-5)		*+*		*+*	*+*
**Secondary exploratory outcomes**					
Patient Health Questionnaire Depression Scale (PHQ-9)		*+*		*+*	*+*
Generalized Anxiety Disorder Scale (GAD-7)		*+*		*+*	*+*
Difficulties in Emotion Regulation Scale (DERS)		*+*		*+*	*+*
Rosenberg Self-Esteem Scale (RSES)		*+*		*+*	*+*
Heidelberg Form for Emotion Regulation Strategies (HFERST)		*+*		*+*	*+*
Ecological Momentary Assessment (EMA)		*+*			*+*
**Other measures**					
Client Sociodemographic Service Receipt Inventory (CSSRI)		*+*		*+*	*+*
Negative Effects Questionnaire (NEQ)				*+*	*+*
Attitudes Towards Online Interventions (APOI)		*+*			*+*
Patients' Therapy Expectation and Evaluation Scale (PATHEV)		*+*		*+*	*+*

#### Primary confirmatory outcomes

2.4.4

•Changes in the frequency of bulimic behaviors within the last 28 days: Based on previous meta-analyses and studies with a similar study design, the changes in the frequency of binge-eating episodes and compensatory behavior over the preceding four weeks were selected as the primary outcomes (Svaldi et al., 2019; Linardon et al., 2020; Wagner et al., 2013; Ruwaard et al., 2013). The *Eating Disorders Examination Questionnaire* (EDE-Q; Hilbert et al., 2007) will be used to assess the number of binge eating episodes and compensatory behaviors within the last 28 days based on the DSM-5 (APA, 2013). The EDE-Q has shown acceptable test-retest reliability (r > .71) regarding the assessment of bulimic behaviors (Rø et al., 2010).

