**Methods:**

The present study will investigate the effectiveness of a web-based self-help intervention for BN in a two-armed randomized controlled trial. Individuals diagnosed with BN (*N* = 152) will be randomly assigned to either (1) an intervention group receiving a 12-week web-based intervention or (2) a waitlist control group with delayed access to the intervention. Further assessments will be scheduled 6 (mid-treatment) and 12 (post-treatment) weeks after baseline. Changes in the number of binge eating episodes and compensatory behaviors will be examined as primary outcomes. Secondary outcomes include global eating pathology, functional impairments, well-being, comorbid psychopathology, self-esteem, and emotion regulation abilities.

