### Objectives and hypotheses

2.1

This study will investigate the effectiveness of a 12-week self-help program, *Selfapy* for BN, which is based on methods of CBT and was designed to directly target BN symptoms as well as topics related to BN such as emotion regulation, stress management, and self-esteem (Knaevelsrud et al., 2016; Sipos and Schweiger, 2016; Tuschen-Caffier and Florin, 2012; Vocks et al., 2005; Waadt et al., 2013). We expect that participants receiving the treatment will show a substantially greater decline in the number of binge eating episodes and the frequency of compensatory behaviors over the 12 weeks of treatment compared to a waitlist control condition. Additionally, we presume that the intervention will be associated with a higher reduction in global eating disorder symptoms. Considering changes in the quality of life, we will further expect a reduction in psychosocial impairments, a higher increase in well-being, and better restoration of work capacity (Agh et al., 2016). Finally, to better understand possible mechanisms of change, we will explore whether the web-based intervention for BN will lead to a greater decline in comorbid psychopathology and more substantial improvements in global self-esteem as well as the ability to regulate emotions after the treatment (Fairburn et al., 2003; Linardon et al., 2019; MacDonald and Trottier, 2019; Svaldi et al., 2019).

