#### Primary and secondary outcome analyses

2.5.1

For the statistical analyses of the effectiveness of the web-based intervention for patients with BN, growth models within a mixed linear models (MLM) framework will be performed. These have the advantage of considering the multi-level data structure of three repeated assessments (level 1) as nested within patients (level 2) and treating the outcome change as a continuous process. Additionally, MLMs have more power when handling missing data than traditional approaches (Hesser, 2015; Kahn and Schneider, 2013; Tasca and Gallop, 2009). To evaluate whether there is a significant treatment × time interaction effect, we will follow a stepwise procedure by running models of increasing complexity (Kahn and Schneider, 2013). First, a random intercept model without predictors will be conducted, then we will add fixed effects of time (study entrance, 6 weeks, 12 weeks) and treatment (IG vs. CG) into the second model. Finally, the treatment × time interaction will be included to evaluate whether the outcome change differs between the IG and the CG. Likelihood ratio tests and the Akaike Information Criterion will be used to compare the fit of these three models. A significant treatment × time-interaction with more substantial changes in the intervention group compared to the waitlist group will confirm the hypotheses (Raudenbush and Bryk, 2002). The magnitude of treatment effects will be estimated following the suggestions for Cohen's *d* by Feingold, 2009, Feingold, 2013.

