### Strengths and challenges

3.1

Based on our goal to evaluate the effectiveness of a web-based intervention, our study was designed as a randomized controlled trial with a waitlist control group maximizing the internal validity of results. To further decrease systematic biases, our randomization will follow the principles of sequence allocation concealment, and systematic pre-treatment differences will be minimized by excluding individuals receiving psychotherapy or pharmacotherapy for BN at baseline (Altman et al., 2001; Gupta, 2011). Further, implementing the web-based intervention into a routine care setting will increase the study's external validity. As such, we enhance the generalizability of our results by allowing participants in our trial to receive care as usual after randomization in both groups. Additionally, participants meeting the criteria for other mental disorders will not be excluded as long as their psychological condition allows them to securely participate in a web-based intervention.

Moreover, we aim at contributing to the research on treatments for BN by investigating changes in both cognitive and behavioral eating disorder symptoms. Network analyses indicate that it is possible to differentiate between various types of BN symptoms (Forrest et al., 2018; Levinson et al., 2017), including the number of binge eating episodes, compensatory behaviors, and global eating pathology. Therefore, we will examine changes in these facets separately to better understand whether and how web-based interventions influence different types of BN symptoms. Weekly assessments and naturalistic EMA data will further increase the ecological validity of results and provide more detailed insights into trajectories of change while reducing retrospective biases (Munsch et al., 2007; Munsch et al., 2019).

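### Two primary outcomes, but one confirmation criterion, one alpha of .05 and a sample size for a single test: the article does not say whether one or both must succeed

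*Protocol article*

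**What the plan says.** The abstract of the protocol article announces two outcomes: "Changes in the number of binge eating episodes and compensatory behaviors will be examined as primary outcomes". Section 2.4.4 repeats the plural: "the changes in the frequency of binge-eating episodes and compensatory behavior over the preceding four weeks were selected as the primary outcomes". Section 2.1 joins them in one expectation, "a substantially greater decline in the number of binge eating episodes and the frequency of compensatory behaviors". Section 3.1, after listing binge eating, compensatory behaviours and global eating pathology, says "we will examine changes in these facets separately".

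The decision rule is in section 2.5.1: "A significant treatment × time-interaction with more substantial changes in the intervention group compared to the waitlist group will confirm the hypotheses". It does not say whether the interaction must be significant for one primary outcome or for both, and no adjusted alpha appears in the article.

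Section 2.6 gives one effect size (d = 0.50), one intraclass correlation (.40), one alpha (.05), one power (.80) and N = 152. Table 2 puts both behaviours in one row under the singular heading "Primary confirmatory outcome".

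**The concern.** With two separately tested primary outcomes, a trial needs a rule for what counts as success. If either is enough, testing each at .05 gives two chances of a false claim. If both are needed, alpha is safe, but the power to meet the criterion is below the power for one outcome.

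The difficulty shows up with a mixed result. If binge episodes improve significantly and compensatory behaviours do not, the article as written allows the team to conclude that effectiveness was confirmed or that it was not. That choice could then be made after the results are known, for the trial's main claim.

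**Working it through.** **Inputs.** From section 2.6: d = 0.50, ICC = .40, alpha = .05, power = .80, N = 152. From section 2.3.1: 1:1 allocation. From section 2.5.1: three assessments (0, 6 and 12 weeks). Not given, and therefore assumed: the correlation ρ between the two test statistics, and d = 0.50 for both outcomes. Sidedness is not stated; it is inferred in step 1.

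**1. Reproduce N = 152.** In a random-intercept growth model with three equally spaced times, the variance of the week-12 change per participant, in baseline SD units, is 2(1 − ICC) = 2 × 0.60 = 1.2. Then

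n per arm = 2 × 1.2 × (1.960 + 0.842)² / 0.50² = 75.4, rounded up to 76, so N = 152.

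This matches exactly, with power .803 at 76 per arm. A one-sided test would give N = 120, so the figure is two-sided. It is the size for one outcome and one test, without dropout.

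**2. Either outcome suffices, each at two-sided .05.**
- Both directions counted, ρ = 0: 1 − 0.95² = 9.75%, the maximum.
- From the bivariate normal, 1 − P(|Z₁| < 1.96, |Z₂| < 1.96): 9.1% at ρ = .5 and 8.3% at ρ = .7.
- Only results favouring the intervention, ρ = 0: 1 − 0.975² = 4.9%, against 2.5% for one test. At ρ = .5 it is 4.5%, and at ρ = .7 it is 4.2%.

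**3. Both outcomes required, each with power .80.** Joint power is P(Z₁ > 1.96, Z₂ > 1.96), which equals the bivariate normal probability Φ₂(0.842, 0.842; ρ).

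| ρ | joint power |
|---|---|
| 0 | .64 |
| .5 | .69 |
| .7 | .71 |
| .9 | .75 |

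It reaches .80 only at ρ = 1. Starting from the exact .803 raises each value by less than .01.

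**4. Power with alpha split.** At N = 152 the expected test statistic is 0.50 / √(1.2 × 2/76) = 2.81. At two-sided .025 the critical value is 2.24, so power is Φ(2.81 − 2.24) = .716, about .72 per outcome. Holm does no worse than this, because the second outcome is tested at .05 once the first is significant.

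**5. Scale of the gap in patients.** For 80% power per outcome at .025, N would be 184. For 80% joint power, N would be 198, 188 or 176 at ρ = 0, .5 or .8.

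**The case against.** The strongest reply is that nothing stated is arithmetically wrong. Section 2.5.1 speaks of hypotheses in the plural, section 2.1 expresses an expectation for each behaviour, and section 3.1 keeps the facets apart. If each outcome supports only its own claim, .05 and .80 are right per outcome, and whether to adjust is a matter of judgement. A single summed count, which the Table 2 row could suggest, would also leave both figures intact. Section 2.6 never claims .80 as joint power. This stands: a reader might infer that the stated alpha or power fails under every reading, and the article does not support that. What remains is that it commits to neither of the readings that would rescue its figures. The plural wording and the separate examination also speak against a summed count.

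Second, the criterion in section 2.5.1 is directional, so 9.75% is not the rate of false confirmation. This also stands: 9.75% is the two-sided familywise rate. In the confirming direction the maximum is 4.9%, but its single-test counterpart is 2.5%, so the near-doubling remains.

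Third, this is a condensed article, and an analysis plan, the R script (Supplement S3) or the supplementary power analyses might hold a rule. That is possible. But the article itself fixes the outcomes, the criterion, alpha and N, and an unseen rule would not turn N = 152 into a two-outcome size. The further power analyses are described as varying dropout, effect size and intraclass correlation, not the number of outcomes.

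The third reply does dispose of a wider inference. A reader might add the five secondary outcomes labelled confirmatory in Table 2 and compute 1 − 0.95⁷ = 30%. The article states neither an alpha nor a testing order for them, and an analysis plan commonly does, so that extension is not supported. Nor is the singular Table 2 heading a competing definition of the primary outcome; it is an editorial slip.

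**Conclusion.** The point holds in this form: the article fixes two separately examined primary outcomes, but its confirmation criterion does not say one or both, and its sample size fits one test. Under an either-outcome rule, two-sided familywise error is up to 9.75%, or up to 4.9% against 2.5% in the confirming direction. Under a both-outcomes rule, joint power is about .64 to .75 instead of .80.

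The error figures rest on each outcome being tested at .05, which is inferred from the only alpha given. The power figures rest on d = 0.50 for both outcomes and on assumed correlations of 0 to .9. The reproduction of N = 152 as a single-outcome size needs none of the assumptions about a second outcome.

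**What to change.** Before allocation is unmasked for analysis, choose one rule and write it into sections 2.4.4 and 2.5.1:

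- **Either outcome may succeed:** test the two primary outcomes with Holm at an overall two-sided 5%. In section 2.6, restate power as about .72 per outcome at .025 with N = 152.
- **Both must succeed:** say so, keep .05 for each, and restate section 2.6 as joint power over a stated range of correlations.

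If separate claims or a single summed count were intended, the text should say that explicitly. Make the Table 2 heading plural if two outcomes are kept.

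The cost is a few sentences and a slightly less favourable stated power. No new data or patients are required.

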### Statistical power and sample size

2.6

Sample size estimations were based on meta-analytic evidence for the effectiveness of psychological interventions for BN (Beintner et al., 2014; Haderlein, 2022; Svaldi et al., 2019). Due to the high heterogeneity of effect sizes ranging from medium to large (Beintner et al., 2014; Haderlein, 2022; Svaldi et al., 2019), the sample size needed to detect at least an effect of medium magnitude was estimated using the R package *powerlmm* (Magnusson, 2018). A power analysis with an effect size of *d* = 0.50, an intraclass-correlation of .40 (Arend and Schäfer, 2019), a power of .80, and an alpha-level of .05 resulted in a required sample of *N* = 152. Further power analyses, including possible dropouts, different effect sizes, and intra-class correlations, can be found in the supplementary materials (Figure S2), strengthening our conclusion that our sample size will be sufficiently large to detect a medium effect under different assumptions.

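### Two primary outcomes but no rule for combining them: the stated power of .80 is per test, about .65–.75 if both must succeed, and a claim on either alone nearly doubles the false-benefit rate

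*Protocol article*

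**What the plan says.** The abstract and section 2.4.4 of the protocol article use the plural. The abstract says: "Changes in the number of binge eating episodes and compensatory behaviors will be examined as primary outcomes". Section 2.4.4 says that "the changes in the frequency of binge-eating episodes and compensatory behavior over the preceding four weeks were selected as the primary outcomes". Section 3.1 lists binge eating, compensatory behaviours and global pathology as distinct symptom types and adds that "we will examine changes in these facets separately to better understand whether and how web-based interventions influence different types of BN symptoms". That rules out a summed composite.

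Table 2 uses the singular heading "Primary confirmatory outcome" over a single row, "Number of Binge Eating and Compensatory Behavior Episodes (EDE-Q".

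Section 2.1 states one joint expectation: treated participants "will show a substantially greater decline in the number of binge eating episodes and the frequency of compensatory behaviors".

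Section 2.5.1 gives the decision rule: "A significant treatment × time-interaction with more substantial changes in the intervention group compared to the waitlist group will confirm the hypotheses".

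Section 2.6 gives one power calculation, with d = 0.50 and an intraclass correlation of .40: "a power of .80, and an alpha-level of .05 resulted in a required sample of" 152. The article states no hierarchy, alpha split, co-primary rule or composite.

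**The concern.** The confirmation rule fits a trial with one primary outcome, and this trial has two. Section 2.1, read literally, requires both interactions to be significant. Section 2.5.1 can be read as satisfied by one. Its plural 'hypotheses' also allows a separate conclusion for each behaviour. These readings have different error rates and different power, and section 2.6 covers only a single test.

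The trial's headline conclusion depends on the choice. If one behaviour is significant and the other is not, the text does not say whether the primary hypothesis is confirmed. The team could then settle the matter after seeing which behaviour responded. A split result is also easy to read as evidence that the intervention works on one symptom type and not the other, although two p-values on either side of .05 do not show that.

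**Working it through.** **Inputs from the article.** d = 0.50, intraclass correlation .40, alpha .05 and power .80 (2.6); three assessments at 0, 6 and 12 weeks (2.5.1); 1:1 allocation (2.3.1); N = 152, so 76 per arm.

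**Assumptions.** The article does not give the correlation r between the two test statistics, so a range of 0 to .9 is shown. The planning d and intraclass correlation are taken to hold for both outcomes. Data are complete.

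**Step 1: reproduce the plan's figure.** Use a random-intercept growth model with time coded 0, 1, 2 and total variance 1.
- Residual variance = 1 − .40 = .60. The squared deviations of time from its mean sum to 2, so the slope variance per patient is .60/2 = .30.
- Slope difference = .50/2 = .25 per interval.
- SE of the slope difference = √(2 × .30/76) = .0889, so the SE of the 12-week contrast is 2 × .0889 = .1777.
- .50/.1777 = 2.814, and power = Φ(2.814 − 1.960) = .803. With 75 per arm it is .798, so 76 per arm is the smallest size that reaches .80.

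N = 152 is therefore reproduced exactly. Alternatives do not give it: a one-sided test needs 120, and a two-sided .025 level needs 184. The figure is for one two-sided .05 test on one outcome, with no allowance for a second.

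**Step 2: both must succeed.** Treat the two test statistics as bivariate normal, each with mean 2.814 and variance 1. Power for both is P(Z₁ > 1.960 and Z₂ > 1.960). At r = 0 this is .803² = .645. The chance of a split result is 2 × (.803 − power for both).

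**Step 3: either suffices, or each is claimed on its own, with no effect on either outcome.** Section 2.5.1 counts only results favouring the intervention, so the relevant error is 1 − P(Z₁ ≤ 1.960 and Z₂ ≤ 1.960). At r = 0 this is 1 − .975² = 4.9%. Counting significance in both directions, it is 1 − .95² = 9.75%.

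| r (assumed) | 0 | .3 | .5 | .7 | .9 |
|---|---|---|---|---|---|
| Power for both | .645 | .671 | .692 | .717 | .754 |
| Split result, both effects equal | .32 | .26 | .22 | .17 | .10 |
| At least one false claim of benefit (single test 2.5%) | 4.9% | 4.8% | 4.5% | 4.2% | 3.5% |
| At least one significant result, either direction (single test 5%) | 9.8% | 9.5% | 9.1% | 8.3% | 7.0% |

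**Step 4: power at the first Holm step (alpha .025).** Φ(2.814 − 2.241) = .716, or .72 per outcome. This is a lower bound, because the second outcome is tested at .05 once the first is rejected.

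**The case against.** Four points can be made for the plan.

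*Separate hypotheses.* Section 2.5.1 speaks of hypotheses in the plural and section 3.1 examines the behaviours separately. Each behaviour may have its own hypothesis, test and conclusion. Then .05 and .80 hold per test, and a split result has a meaning. This stands as an available reading, so it cannot be said that no reading delivers the stated alpha and power. But the article does not adopt it, section 2.1 words one joint expectation, and under it the chance of at least one false primary claim still rises as in Step 3.

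*Direction.* A reader might infer that the plan carries a 7–10% risk of falsely claiming benefit. It does not. Section 2.5.1 requires the difference to favour the intervention, so the rate is 3.5–4.9% and stays below 5%. The comparison is with 2.5% for one such test, so the proportional inflation is about the same.

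*Effect size.* A reader might also infer that the trial is simply underpowered. Section 2.6 sizes for at least a medium effect and cites effects from medium to large. With the same formula, d = .57 on both outcomes gives joint power of about .80 even at r = 0, and d = .60 gives .85–.90. The shortfall holds at the planning value, which is the value for which .80 is quoted.

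*Unseen material.* The .05 appears only in the power section, and the R script and further power analyses are in supplements not shown. A rule may be stated there. The article's own rule, Table 2 and section 2.4.4 would still need reconciling. The article also does not propose comparing the two p-values; that is a foreseeable misreading of a split result, not a planned analysis.

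**Conclusion.** The point holds. The article fixes a confirmation rule and a sample size for one test while naming two primary outcomes. At d = .50 and an intraclass correlation of .40 for both, with complete data, .80 is the power of each test. Power for both is about .65–.75 for assumed correlations of 0 to .9. A split result would occur with probability .10 to .32 even if both effects were equal, and the rule does not say what it means for the primary hypothesis. If a single success can be claimed, the false-benefit rate is 3.5–4.9% against 2.5%. The size of each figure depends on the unstated correlation, but no correlation short of 1 brings joint power back to the per-test value or removes the inflation.

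**What to change.** State in sections 2.4.4 and 2.5.1 and in Table 2 that there are two primary outcomes, each with its own model, and choose one rule before the unmasked analysis.

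- **(a) Both required.** The primary hypothesis is confirmed only if both interactions favour the intervention at two-sided .05. No alpha adjustment is needed. A split result does not confirm it, and the one significant outcome is reported as non-confirmatory. Without that last condition, rule (a) becomes an unadjusted either-suffices rule. Section 2.6 should then give power as .80 per outcome and about .65–.75 for both, with the assumed correlation stated.
- **(b) One behaviour may be claimed alone.** Apply Holm across the two interactions and restate power in section 2.6 as at least .72 per outcome.

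Under either rule, claim a different effect on the two behaviours only from a direct test of that difference.

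The cost is wording in four places and a less favourable stated power. No extra patients or data are needed.
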